**Methods/Design:**

The study is an open, non-inferiority randomised controlled trial with data collected at baseline, 6 and 12 months. Participants are identified from new patients on hospital-based diabetes outpatient clinic waiting lists and new GP referrals. Eligible consenting patients are randomised to either a community practice site (intervention) or a hospital site (usual care). In the intervention model, medical care is led by a GP Clinical Fellow in partnership with an Endocrinologist. Quantitative measures include clinical indicators with HbA1c as the primary outcome; patient-reported outcomes include health-related quality of life, mental health and satisfaction with care. Qualitative methods will be used to explore the perspectives and experiences of patients and providers regarding the new model of care. An economic evaluation will also be undertaken.

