## Methods/Design

### Study design

The study uses a non-inferiority randomised controlled trial design. A mixed methods approach of data collection including quantitative and qualitative methods is used. Non-inferiority trials are designed to show that a novel treatment is at least no worse than a standard treatment in terms of some primary clinical endpoint
[25], in this case HbA1c. Accordingly, the primary hypothesis is that glycaemic control of patients with T2DM who have their treatment delivered through management by a community-based multidisciplinary integrated primary-secondary healthcare team (including an Endocrinologist) using protocol driven care, will be comparable to glycaemic control achieved in a hospital outpatient clinic setting.

The research questions include:

1. What is the impact of the new model of care on glycaemic control and other clinical indicators compared to usual care?

2. What is the impact of the new model of care on patient-reported outcomes compared to usual care?

3. What is the cost-effectiveness and cost utility of the new model of care compared to usual care?

4. What are the perspectives and experiences of patients and health professionals regarding the new model of care?

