### Sample size and power calculation

Sample size is based on the primary endpoint of HbA1c using an alpha = 0.05 and power = 80%. Based on findings from the pilot study, the sample size calculation used a pooled standard deviation in HbA1c of 1.7%. The non-inferiority margin is -0.4% and the true difference between the groups in HbA1c at 12 months is predicted to be 0.1%
[26]. A randomisation ratio of 3:1 (intervention to usual) has been chosen so that the clinics at the intervention sites maintain reasonable and sustainable capacity
[16]. Based on the above assumptions and adding a level of attrition of 20% between baseline and 12-month follow-up in both groups, the total sample size is estimated at 456.

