### Statistical analysis plan

Baseline demographic, psychosocial and clinical characteristics of participants will be summarised and compared for differences between the intervention and usual care groups. Characteristics of participants who complete and those who withdraw will be compared.

The analysis of the primary outcome (HbA1c) will be assessed using linear regression; secondary outcomes measures will be assessed using either linear regression (continuous outcomes) or logistic regression (binary outcomes). To adjust for potential between-group imbalance, the baseline score of the outcome of interest will be included as a covariate in models. Site allocation will also be included in models as a covariate.

All analyses will be conducted on an intention-to-treat basis. Statistical significance will be based on two-tailed tests, with *P* <0.05 considered significant.

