## Discussion

We present a protocol for the study design and methods to evaluate a new model of diabetes care in the community through multidisciplinary collaboration and integration across the primary-secondary interface. The model of care aims to improve the quality and safety of healthcare at the interface between hospital- and community-based primary care for patients with complex diabetes. This model has been pilot-tested in a community chronic disease management service, and the results indicated benefits for diabetes patients in comparison with usual care at the hospital diabetes outpatient clinic
[23,26]. The current study builds on the promising results of Russell and colleagues’ study
[23] in a larger, more robust research design and addresses the methodological issues identified in their study which utilised a non-randomised convenience sampling method. Non-inferiority randomised controlled trials are usually conducted on the premise that there is some other advantage of the treatment such as a reduction in waiting list times, reduced costs or improved access
[34].

The study is important because it will provide empirical evidence about the impact on health outcomes, patient and clinician satisfaction, and economic outcomes of the improved integration of services. The results will also help us to understand the perspectives and experiences of both patients and health providers regarding the new model of care. Using a mixed methods approach will enhance the quality of the findings by enabling us to examine the model from different perspectives. It will also provide insights regarding contextual factors affecting the acceptability of the model and how it may be implemented in the future. In addition, selection bias is avoided by randomising at the level of individual patients.

However, some limitations of the study need to be considered. Participant retention in this longitudinal study will be sensitive to patient medical conditions, patient motivation as well as patient relocation out of the study area. There may be some patient issues around willingness to participate if randomly allocated to a clinic setting that is difficult to attend due to distance travel cost, and so on. Additionally, self-reported data on service use may be under-reported

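### Intention-to-treat is the only analysis basis in this open non-inferiority trial, so dilution from switching or balanced non-attendance could go unseen

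*Protocol article*

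**What the plan says.** The Study design section states: "The study uses a non-inferiority randomised controlled trial design". The abstract adds that the trial is open. The Statistical analysis plan section fixes one analysis basis for everything: "All analyses will be conducted on an intention-to-treat basis". No per-protocol, as-treated or other adherence-based analysis of HbA1c appears in the article. The nearest item is a descriptive comparison of completers with those who withdraw, which does not test non-inferiority.

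The Discussion recognises that the allocated clinic may be a problem for some patients: "There may be some patient issues around willingness to participate if randomly allocated to a clinic setting that is difficult to attend". It also refers in general terms to the weaknesses of non-inferiority trials, without linking them to an analysis. No rate of switching or non-attendance is given.

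**The concern.** In a superiority trial, dilution of the treatment contrast usually works against the sponsor's claim. In a non-inferiority trial it can work for it. If patients allocated to the community service are in fact treated at the hospital, or if similar shares of both arms never attend, the ITT difference shrinks towards zero and a poorer model is more easily declared non-inferior.

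Several features of the design make departures from allocation plausible:

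- Participants come from hospital referrals and waiting lists, and 3:1 allocation sends most of them to a different service.
- Appointment details follow randomisation, so some patients may never start the allocated care.
- General practice records fill gaps in clinical data (Quantitative study data), so a patient who did not attend can still contribute an HbA1c value.

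At stake is how a positive result can be read. With ITT alone, nothing planned would help to separate comparable care from diluted care.

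**Working it through.** **Inputs from the article.** Sample size and power calculation: "using an alpha = 0.05 and power = 80" per cent; "pooled standard deviation in HbA1c of 1.7" per cent; "The non-inferiority margin is -0.4% and the true difference between the groups in HbA1c at 12 months is predicted to be 0.1" per cent; attrition 20%; total 456. Recruitment and randomisation: 3:1 allocation. Below, a difference is intervention minus usual care in HbA1c, so a positive value means the intervention is worse and the margin lies at 0.4%.

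**Reproducing 456.** With one-sided alpha 0.05 and the 0.1% difference favouring the intervention, the distance to the margin is 0.5:

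n(control) = (1 + 1/3) × [1.7 × (1.645 + 0.842) / 0.5]² = 95.3

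Then 95 × 4 = 380 and 380 × 1.2 = 456. The stated total reproduces, and the present point does not rest on an error in it. The analysis section says "Statistical significance will be based on two-tailed tests" at 0.05. Read as a 95% interval against the margin, that is one-sided 2.5%, so both levels are shown.

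**Standard error.** With 80% of 456 evaluable, 364.8 patients split into 91.2 and 273.6:

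SE = 1.7 × √(1/91.2 + 1/273.6) = 0.2056

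**Switching (assumed rates).** Let the true difference be 0.4% in those who receive the new model, and let a share c of intervention patients receive usual care. Then:

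ITT difference = 0.4 × (1 − c)

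P(declare non-inferior) = Φ[(0.4 − 0.4(1 − c)) / 0.2056 − z]

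| c (assumed) | ITT difference | one-sided 5% (z = 1.645) | one-sided 2.5% (z = 1.96) |
|---|---|---|---|
| 0 | 0.40 | 5.0% | 2.5% |
| 5% | 0.38 | 6.1% | 3.1% |
| 10% | 0.36 | 7.3% | 3.9% |
| 20% | 0.32 | 10.5% | 5.8% |
| 30% | 0.28 | 14.4% | 8.4% |

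For c = 20% at one-sided 5%: 0.08 / 0.2056 = 0.389; 0.389 − 1.645 = −1.256; Φ = 10.5%.

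**Non-attendance (assumed 20%, non-attenders 0.8% worse than usual care, one-sided 5%).**

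- Both arms equally: (0.8 × 0.4 + 0.2 × 0.8) − 0.2 × 0.8 = 0.32, the same dilution as 20% switching, 10.5%.
- Usual care arm only: 0.4 − 0.2 × 0.8 = 0.24; Φ(0.16 / 0.2056 − 1.645) = about 19%.
- Intervention arm only: 0.8 × 0.4 + 0.2 × 0.8 = 0.48; Φ(−0.08 / 0.2056 − 1.645) = about 2%.

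The direction therefore depends on the pattern of departures.

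**Power of a per-protocol analysis.** Excluding a share e of completers equally from both arms, power = Φ[0.5 × √(1 − e) / 0.2056 − z]:

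| e (assumed) | one-sided 5% | one-sided 2.5% |
|---|---|---|
| 0 | 78% | 68% |
| 10% | 75% | 64% |
| 20% | 70% | 59% |
| 30% | 65% | 53% |

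**The case against.** The case for leaving ITT alone is serious. The trial compares two ways of delivering a service, and attendance is arguably part of what each way achieves. For the effect of being allocated to a service, the ITT test keeps its nominal error rate. The inflation above concerns the effect in those who receive the model. This stands, and it is why ITT should remain primary. The primary hypothesis, however, concerns patients treated through the community team, so the second question is also of interest.

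A reader might infer that ITT is always anti-conservative here. The intervention-only example shows that it is not.

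A reader might also infer that the Discussion predicts crossover. It speaks of willingness and difficulty of attendance, which may mean refusal, withdrawal or non-attendance. The article describes no transfer to the other arm after randomisation. The hospital care offered to patients who decline the study is a different matter, and eligibility requires residence in a community service's catchment. Some non-attenders will have no 12-month HbA1c and will count as attrition, for which 20% is allowed, rather than as dilution.

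Finally, a short article may leave supporting populations to a fuller plan. That would answer an omission. Here the sentence covers all analyses, so as written it leaves no place for an adherence-based one.

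**Conclusion.** The point holds in a limited form. The stated rule is not wrong as a primary analysis, but it provides no check against a form of dilution that can favour non-inferiority in an open trial. If 10% to 30% of intervention patients received usual care and the model were worse by the full margin in those treated, false non-inferiority would be about 7.3% to 14.4% instead of 5%, or 3.9% to 8.4% instead of 2.5%. These figures rest on assumed switching rates, the article's SD of 1.7%, 20% attrition and a normal approximation without covariate adjustment. The documents do not support a claim that such switching will occur, or that the result will be biased in one known direction. This is a worthwhile, inexpensive improvement.

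**What to change.** Amend the sentence so that ITT remains the primary analysis and a supporting per-protocol analysis is pre-specified:

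- Outcome and model: 12-month HbA1c against the same 0.4% margin, with the same covariates as the primary model.
- Population: patients who attended the medical appointment at the allocated type of service and did not transfer to the other arm's service. Discharge to the usual GP under the model would not count as a transfer.
- Reporting: exclusions by arm and by reason, and a required discussion of consistency between the two analyses before non-inferiority is concluded.

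The data are already planned: service use and discharge dates under Clinical indicators, attendance under Economic indicators. The Trial status section reports 111 of the 456 patients recruited, so at that stage the rule could still be set well before follow-up was complete.

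The cost is one further analysis, with real limits. The per-protocol set loses the protection of randomisation. In an open trial attendance may itself depend on arm, so the set is not automatically conservative. Its power is also lower, as shown above. Requiring both analyses to succeed would add to the power loss, so the analysis should be supporting and not a mandatory joint criterion.

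### The only stated test for the primary outcome is a two-tailed P<0.05 test that never uses the 0.4% margin, so it does not match the non-inferiority design or the sample size

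*Protocol article*

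**What the plan says.** The protocol article's Study design section is explicit: "The study uses a non-inferiority randomised controlled trial design". It words the primary hypothesis as glycaemic control that "will be comparable to glycaemic control achieved in a hospital outpatient clinic setting", without mentioning a margin.

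The margin appears once, under Sample size and power calculation: "The non-inferiority margin is -0.4" (in % HbA1c). The same section says "Sample size is based on the primary endpoint of HbA1c using an alpha = 0.05 and power = 80" (per cent), without saying whether alpha is one- or two-sided. It also gives an expected true difference of 0.1% without a direction.

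The section headed Statistical analysis plan names linear regression for HbA1c, with baseline value and site as covariates, on an intention-to-treat basis. Its only decision rule is "Statistical significance will be based on two-tailed tests", with P<0.05 as the threshold. The rule is not limited to secondary outcomes. The section mentions neither the margin nor a confidence limit.

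**The concern.** A non-inferiority claim is one-directional and is made against the margin: the data must rule out a deficit of 0.4% or more. An ordinary two-tailed regression P value answers a different question, whether the difference is zero.

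Under that rule, P<0.05 would show that one arm is better than the other. A significant result in favour of the intervention would imply non-inferiority, but the trial is not powered for it. P>0.05 would only show that a difference had not been demonstrated, which is not evidence that the new model is no worse than usual care by the margin. The rule therefore gives no route to the primary conclusion in the situation the trial was built for, and it leaves room for a non-significant result to be reported as comparable.

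**Working it through.** **Inputs, all from Sample size and power calculation:** SD 1.7%, margin 0.4%, expected difference 0.1%, power 80%, alpha 0.05, allocation 3:1, attrition 20%, total 456.

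**1. Reproduce 456.** With n usual-care patients and 3n intervention patients, the variance of the difference is SD² × (4/3)/n. If the 0.1% favours the intervention, the distance to the margin is 0.4 + 0.1 = 0.5. At one-sided alpha 0.05:

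n = (4/3) × [1.7 × (1.645 + 0.842)/0.5]² = 95.3, total 381.

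Multiplying by 1.2 gives 457, and 95 + 285 = 380 gives 380 × 1.2 = 456 exactly. The variants tried that do not give 456 are:

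- Dividing by 0.8 instead of multiplying by 1.2: 477 (480 with rounding up).
- One-sided 0.025: 484 evaluable, then 581 (× 1.2) or 605 (÷ 0.8).
- True difference of zero: 716 to 950.
- The 0.1% favouring usual care: 1272 to 1685.

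So the trial was sized for a one-sided 0.05 test against the margin, which is not the test in the analysis section.

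**2. Standard error at the planned size.** 456 × 0.8 = 364.8 analysed, split 273.6 and 91.2.

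SE = 1.7 × √(1/273.6 + 1/91.2) = 0.206.

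**3. Chance that two-tailed P>0.05 when the intervention is truly worse by d:** Φ(1.96 − d/SE) − Φ(−1.96 − d/SE).

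- d = 0.4, about 365 analysed: 50.6%.
- d = 0.4, 380 analysed: 49.0%.
- d = 0.4, all 456 analysed (SE 0.184): 41.5%.
- d = 0.3, about 365 analysed: 69%.

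**4. Allowing for baseline adjustment.** If 1.7 is the unadjusted SD, adjustment multiplies the SE by √(1 − r²). The protocol does not give r, so these values are assumptions. At d = 0.4 and about 365 analysed:

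| r | SE | P(non-significant) |
|---|---|---|
| 0.3 | 0.196 | 46.8% |
| 0.5 | 0.178 | 38.7% |
| 0.7 | 0.147 | 22.2% |

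A rule based on the margin holds the corresponding error at 2.5% (two-sided 95% interval) or 5% (two-sided 90% interval).

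**5. What the two-tailed rule yields if the design assumption is true.** With a true difference of 0.1%, d/SE = 0.1/0.206 = 0.49, and P<0.05 (either direction) occurs in 7.8% of trials. A just non-significant deficit of about 0.40 (1.96 × 0.206) would have an upper 95% limit near 0.81, twice the margin.

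**6. Power of a margin-based rule** with about 365 analysed and a true 0.1% benefit: Φ(0.5/SE − z).

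- One-sided 0.05: Φ(2.43 − 1.645) = 78%.
- One-sided 0.025: Φ(2.43 − 1.96) = 68%.

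**The case against.** The sentence on two-tailed tests closes a section covering many secondary outcomes. It writes out no null hypothesis for HbA1c and could be taken as merely setting a significance level, since two-sided 5% corresponds to a 95% interval. The article does state the design, endpoint, margin and model, and a condensed article may leave the formal confidence-limit criterion to a fuller document that is not shown.

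Mere silence about that criterion would be excused on this ground. But the article does state a rule, the rule covers the primary regression, and on its natural reading it belongs to a trial of difference. Read instead as a level for a 95% interval, it still conflicts with the sample size, which is reproduced only at one-sided 0.05.

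Three stronger readings are tempting and are not supported:

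- *That the investigators will treat P>0.05 as proof of comparability.* The protocol nowhere says so. The wording of the hypothesis leaves room for it, no more.
- *That the error rate is simply one half.* That figure needs a true deficit exactly at the margin, the unadjusted SD and 20% attrition. The protocol prescribes baseline adjustment, which could lower it substantially.
- *That an observed difference of zero would miss the margin.* The unadjusted 95% half-width is 0.403, but if 1.7 is the unadjusted SD, a baseline correlation above about 0.12 brings it below 0.400.

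**Conclusion.** The point holds as a conflict between a stated rule and the stated design. Followed as written, the analysis section tests the wrong hypothesis for the primary outcome and does not use the margin on which the trial was sized.

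If a non-significant result were taken as success, the chance of passing a model truly worse by 0.4% would be about 51% on the plan's own SD and attrition. It ranges down to 22% over the attrition and correlation assumptions shown. Every value is well above the 2.5% or 5% of a margin-based rule. These figures measure the consequence of a reading that the protocol permits but does not announce.

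There is a linked inconsistency in alpha: one-sided 0.05 behind the sample size, two-tailed 0.05 in the analysis. That the 0.1% favours the intervention is inferred from reproducing 456; the text does not say so. The matter should be settled before outcomes are analysed, because it determines the trial's primary conclusion.

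**What to change.** In the Statistical analysis plan section, replace the rule for the primary outcome with one of this form: non-inferiority is concluded if the upper limit of the two-sided confidence interval (level stated) for the baseline-adjusted difference in 12-month HbA1c, intervention minus usual care, is below +0.4 percentage points. State the sign convention: the protocol writes the margin as negative, whereas with this subtraction a deficit for the intervention is positive. Restrict two-tailed P<0.05 to secondary outcomes and to any superiority test made after non-inferiority is met.

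Choose the interval level knowingly and make the two sections agree:

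- A 90% interval (one-sided 0.05) matches the calculation behind 456 and gives about 78% power with 365 analysed.
- A 95% interval is stricter. The stated power should then be given as about 68% before any gain from baseline adjustment. Restoring 80% without that gain would need 484 evaluable, or 484/0.8 = 605 randomised.

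Also state that the expected 0.1% favours the intervention, if that is what was meant. The cost is a few sentences and a slightly less favourable stated power. No new data or patients are needed for the correction itself.

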### Qualitative data analysis

All interviews and focus groups will be conducted by experienced qualitative researchers and audio-taped for transcription. The transcripts will be analysed thematically
[33] to identify themes and patterns in order to understand and illustrate the expectations, perceptions and experiences of patients and health professionals who use the intervention model of care. Deviant and negative cases will be included and all themes will be verified through constant comparison and team discussion.

### Ethics

The study has been granted ethical approval by the Human Research Ethics Committee of Metro South Health Service District, Centres for Health Research of Princess Alexandra Hospital and the Medical Research Ethics Committee at The University of Queensland.

## Discussion

We present a protocol for the study design and methods to evaluate a new model of diabetes care in the community through multidisciplinary collaboration and integration across the primary-secondary interface. The model of care aims to improve the quality and safety of healthcare at the interface between hospital- and community-based primary care for patients with complex diabetes. This model has been pilot-tested in a community chronic disease management service, and the results indicated benefits for diabetes patients in comparison with usual care at the hospital diabetes outpatient clinic
[23,26]. The current study builds on the promising results of Russell and colleagues’ study
[23] in a larger, more robust research design and addresses the methodological issues identified in their study which utilised a non-randomised convenience sampling method. Non-inferiority randomised controlled trials are usually conducted on the premise that there is some other advantage of the treatment such as a reduction in waiting list times, reduced costs or improved access
[34].

The study is important because it will provide empirical evidence about the impact on health outcomes, patient and clinician satisfaction, and economic outcomes of the improved integration of services. The results will also help us to understand the perspectives and experiences of both patients and health providers regarding the new model of care. Using a mixed methods approach will enhance the quality of the findings by enabling us to examine the model from different perspectives. It will also provide insights regarding contextual factors affecting the acceptability of the model and how it may be implemented in the future. In addition, selection bias is avoided by randomising at the level of individual patients.

However, some limitations of the study need to be considered. Participant retention in this longitudinal study will be sensitive to patient medical conditions, patient motivation as well as patient relocation out of the study area. There may be some patient issues around willingness to participate if randomly allocated to a clinic setting that is difficult to attend due to distance travel cost, and so on. Additionally, self-reported data on service use may be under-reported
[35,36]. Nevertheless, every effort has been made to present and structure the patient information sheet and survey for this present study in a simple and straightforward format. Furthermore we have conducted pre-testing and pilot studies to refine the survey in an attempt to minimise item non-response and facilitate a good overall response rate
[37]. In addition, efforts will be also made through rigorous implementation of recruitment and survey strategies during the data collection process, and using a best-estimation technique for item non-response to reduce missing items. Also, we cannot rule out the possibility that change in the outcomes could in part be accounted for by an observer effect whereby participants modify their behaviour, in particular their self-care and self-management regimes, in response to being involved in the trial (for example, the intensity of the study assessment) rather than in response to being involved in the model of care. To minimise this effect, we have included both a control and intervention group in the study design that undertake the same measures. Patient surveys are incorporated into the process of patient care, and are distributed to patients by Registered Nurses at the clinical study sites for patients to self-complete. Ideally, if the model of care is shown to be effective and is subsequently embedded in usual clinical practice, routinely collected clinical data could be used to reassess patient outcomes in the longer term. Finally, a longer follow-up period would further elucidate the potential to investigate the sustainability of any observed effects. The results will need to be interpreted with consideration of the inherent weaknesses of non-inferiority trials
[25].

There are some challenges around planning and setting up such a complex randomised controlled trial within a health services delivery setting, such as governance issues, the building of relationships with key research stakeholders, and adjustments to planned research delivery to accommodate healthcare reform changes in hospital and community care. Nevertheless, better integration of primary and secondary care and ‘ending the blame game’ between Commonwealth and State-funded healthcare has been a key element of Australian health reform since 2007. Better integrated care leading to improved quality outcomes for communities has been underlined repeatedly by the National Health and Hospitals Reform Commission, the Council of Australian Government’s Reform Council, the National Primary Health Care Strategy, the National E-Health Transition Authority and Health Workforce Australia
[38]. To date, there have been few rigorous international publications to guide success in the area. Our randomised non-inferiority trial, based around a successful cohort pilot, will progress international learning in the area of chronic disease. If effective, the intervention could be applied to other chronic conditions and extended nationwide for integrated care delivery in the future.

